### Security

AEs will be recorded during each operation. The following conditions are defined as SAEs: 1) aggravated illness requiring hospitalisation; 2) disability; and 3) other major medical events. In the event of an SAE, the lead investigator will report to the sponsor within 24 days, and the investigator will intervene as a third party to evaluate whether the AEs are connected to the intervention. If necessary, the appropriate medical services should be provided when the victim asks for compensation. Participants will be withdrawn if the AEs are too severe for them to continue with the trial. However, participants need not withdraw if the AE is unrelated to the intervention or is not a SAE, with respect to the individual wishes of the participants.

Given the safety of rESWT, no safe end point will be predefined because this is considered impossible. However, all AEs will be documented as evidence for safety assessment. Meanwhile, a meaningful number of adverse reactions will be observed.

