### Interventions

The time of interventions will be within the first 48 h of the menstrual period (Fig. 2). Trained and qualified practitioners from the Ministry of Health of the People’s Republic of China will perform real and sham rESWT therapy on the participants. Before the intervention, the myofascial trigger points in the abdominal muscles (Fig. 3) will be clinically located by the clinician, and ultrasound coupling gel will be applied on the lower abdominal skin surface (Fig. 2). In the real rESWT group, therapists will use radial shock wave devices based on previous experience to apply 5000 impulses of radial shock waves with a pressure of 1.5 bar at a rate of 10–14 impulses per second for each participant (STORZ MEDICAL AG, MASTERPULS® MP100, C15, diameter 15 mm, Switzerland) (Fig. 4 and Table 2) [9, 10]. Patients in the sham therapy control group will receive placebo intervention with the same sound but no energy input [17]. Moreover, any other treatment to improve menstrual pain will be restricted in both the real and sham rESWT groups during the trial.

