**Fig. 4 Fig4:**
[figure not shown]
Description of the shockwave instrument. Above is the front view of the shockwave instrument (model: MASTERPULS MP100), and below is the side view of the treatment handle (model: R-SW handpiece)

**Table 2 Tab2:** Details of rESWT intervention

Item	Detail	Description
rESWT rationale	Type of shock wave	Pneumatic ballistic extracorporeal shock wave therapy
	Reasoning for treatment	The best treatment option was selected according to our previous study results and other clinical trials of rESWT for primary dysmenorrhoea
	Extent to which treatment varies	None
Details of rESWT	Number of treatment sites per subject	6
	Names of points used	Attachment point of rectus abdominis above the symphysis pubis (bilateral) (blue dot in Fig. 3)
		Intersection of the anterior superior iliac spine with the outer margin of the rectus abdominis (bilateral) (yellow dot in Fig. 3)
		The anterior superior iliac spine shifts inward by approximately 2 cm along the line (bilateral) (location of the red dot in Fig. 3)
	Shock wave intensity	1.5–2.0 bar
	Shock wave frequency	10–14 Hz
	Number of hits from each site	600 times
	Response sought	None
Treatment regimen	Number of treatment sessions	1 time
	Treatment time	Within 48 h of menstruating
Other components of treatment	Details of other interventions administered to the rESWT group	None
	Setting and context of the treatment	Hospital rehabilitation section, outpatient department
Background of practitioner	Profile of the therapist	Specialist in rehabilitation medicine or a resident of more than 1 year under the guidance of the specialist in rehabilitation medicine
Control or comparator	Rationale for the control or comparator in the context of the research question	As a placebo control, a non-energetic sham rESWT was used

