### Management of study data

In this trial, data managers will use the double-entry method to input data into the Microsoft Excel 2016 software and establish an electronic database. They will also use password protection. The Clinical Research Center of Xuhui District Central Hospital in Shanghai will conduct regular monitoring tests to ensure the integrity and authenticity of all data. Interim data analysis should not be undertaken for any reason at any time. To ensure the confidentiality of the participants, all patients will be made pseudonymous using study identification numbers. Moreover, all researchers will have access to the final database.

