### Quality control and monitoring

This study aims to explore the efficacy and mechanism of rESWT for PDM. The Data Monitoring Board is considered a non-essential safety consideration at this time, and similar studies often apply the same approach. Owing to the heavy variety of data tasks, inspectors must monitor the data. According to the actual situation, they will conduct evaluation of the source documents, including medical document charts, related reports and AE records, as well as additional documents, such as agreements, informed consent forms and pathological report forms, all of which will also be under unified management.

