### Trial status

The study was registered with the Chinese Clinical Trial Register (ChiCTR1900020678) on 13 January 2019. Participant recruited was started on 31 January 2019. At the time of submission, seven patients have been selected into our centre. Recruitment is expected to be completed around December 2019.

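### The only stated deadline for reporting a serious adverse event to the sponsor is 24 days, probably a slip in the unit, and it should be checked against the approved protocol and corrected

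*Protocol article*

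**What the plan says.** The Security section of the protocol article defines SAEs as worsening illness that needs hospital admission, disability, or another major medical event. It then sets the reporting rule: after an SAE, "the lead investigator will report to the sponsor within 24 days". The same sentence adds that "the investigator will intervene as a third party to evaluate whether the AEs are connected to the intervention".

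No other section gives a time limit for telling the sponsor about an SAE. The surrounding safety provisions are these:

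- **Monitoring board:** under Quality control and monitoring, "The Data Monitoring Board is considered a non-essential safety consideration at this time".
- **Safety end point:** the Security section says that none is predefined.
- **Action after an SAE:** Termination criteria and Security deal with withdrawing the affected participant. The article gives no rule for pausing enrolment.
- **Collection of adverse events:** Security has them recorded at each operation, and Table 1 marks them at close-out.
- **Other oversight:** Management of study data provides for regular monitoring of data integrity by a clinical research centre. Quality control and monitoring has inspectors review source documents, including adverse event records. Neither section gives a frequency.

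On timing, Trial status puts the start of recruitment at 31 January 2019 and adds: "Recruitment is expected to be completed around December 2019". Seven patients had been selected at the time of submission.

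**The concern.** A deadline for reporting serious harm lets the sponsor consider whether others should go on being exposed. A limit of 24 days serves that purpose poorly for events that include hospitalisation and disability. The number suggests that hours were meant, but nothing else in the article states an SAE time limit that would settle the matter.

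The sentence is a rule that staff are meant to follow. It is also a stated figure rather than a detail left out of a condensed article, so the existence of a fuller protocol does not explain it away. With no monitoring board and no predefined safety end point, it is the one time-limited step in the article by which the sponsor learns of serious harm. Further participants could be treated while an SAE report was pending and still within the rule.

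**Working it through.** The 24-day limit is stated text, so there is no plan figure to reproduce. The check asks how many further participants could enter the trial within that window.

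**Inputs**

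- Reporting limit: 24 days (Security).
- Planned size: 36 participants, 18 per group, allocated 1:1 (Sample size calculation; Design).
- Recruitment: from 31 January 2019 to some point in December 2019 (Trial status). To 1 December is 304 days; to 31 December is 334 days.
- Treatment: one session (Table 2), in the first 48 hours of menstruation (Interventions).

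**Assumptions:** uniform accrual, no pause on site, the full window used, and enrolment standing in for treatment.

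**Expected entrants during the window** = 36 / recruitment days × 24

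- 334 days: 36 / 334 × 24 = 2.59, which is 2.59 / 36 = 7.2% of the trial.
- 304 days: 36 / 304 × 24 = 2.84, which is 2.84 / 36 = 7.9% of the trial.

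**Expected entrants on active rESWT** (half, by 1:1 allocation)

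- 334 days: 2.59 / 2 = 1.29.
- 304 days: 2.84 / 2 = 1.42.

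**Chance of at least one further entrant**, treating arrivals as Poisson: 1 − exp(−mean)

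| Recruitment days | Any arm | Active arm |
|---|---|---|
| 334 | 1 − exp(−2.59) = 0.925 | 1 − exp(−1.29) = 0.726 |
| 304 | 1 − exp(−2.84) = 0.942 | 1 − exp(−1.42) = 0.759 |

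**Sensitivity to the number recruited.** With 30 participants, the number before the drop-out allowance, the expected count is 30 / 334 × 24 = 2.16 to 30 / 304 × 24 = 2.37. The chance of at least one entrant is then 0.884 to 0.906.

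**If the unit were hours.** The expected count over 24 hours is 36 / 334 = 0.11 to 36 / 304 = 0.12 participants, so the choice of unit changes the figure 24-fold.

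These counts are averages. They are upper limits only in the sense that they use the whole window; by chance, more or fewer participants could enter.

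**The case against.** The strongest reply is that this is a one-word slip in a journal article. The full protocol approved by the ethics committee may carry the intended figure, and the article cannot show that staff actually work to 24 days. That is fair, and it limits the point to the printed rule. It does not remove the point, because the published sentence is wrong if hours were meant and needs justification if days were meant.

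A reader might also infer several stronger things that the article does not support:

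- **That nobody would know of the event for 24 days.** The lead investigator makes the report and an investigator assesses causality, so the people running the trial already know. Only the sponsor's knowledge can lag.
- **That this report is the sponsor's only route to learning of harm.** Inspectors review adverse event records and a research centre monitors the data. With no frequency given, neither can be counted on as a timely backstop, but neither can be ruled out as a route. The supported wording is the only route with a time limit.
- **That further participants would be treated.** Twenty-four days is a maximum, so the supported word is could. About half of those entering would receive sham without energy input.
- **That the risk is raised because the use is new.** The Background cites earlier studies of rESWT in dysmenorrhoea, one of them reporting no adverse events over 6 months of follow-up, and Table 2 bases the regimen on earlier work. The Discussion claims to be the first randomised trial of a set of effects, not the first use.
- **That the ban on interim analysis makes matters worse.** The Management of study data section does say "Interim data analysis should not be undertaken for any reason at any time", but reporting an individual SAE does not depend on an interim look.
- **That the window matters because it is nearly as long as the 27 to 32 day cycle required for eligibility.** Treatment is a single session, so a late report cannot prolong the affected participant's own exposure. The consequence is for later participants.

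**Conclusion.** The point holds as a defect in a stated safety rule. The article allows up to 24 days to tell the sponsor of an SAE and gives no other SAE time limit. That the unit should be hours is likely, but it is an assumption.

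If the full window were used, about 2.6 to 2.8 further participants (7% to 8% of the trial), 1.3 to 1.4 of them on active rESWT, would be expected to enter before the sponsor must be told. This rests on the assumptions listed with the calculation and is an illustration of the most that the rule permits at the planned pace. It is not a forecast, and it is not evidence that any report was late. The need to correct the sentence comes from the printed limit itself and does not depend on these counts.

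**What to change.** Check the figure and the unit in the Security section against the protocol approved under 2018043, then correct the sentence to the expedited window approved there. If the approved text also says 24 days, the sponsor should justify or amend it. Notify site staff of the corrected rule, and check that any SAE so far was reported within the approved window. The article is dated 11 February 2020, after the planned end of recruitment, so this look back matters even if enrolment has closed.

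The cost is a short published correction, one notice to staff and a brief review of any SAE reports. The design, sample size and analysis are unaffected.

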### Management of study data

In this trial, data managers will use the double-entry method to input data into the Microsoft Excel 2016 software and establish an electronic database. They will also use password protection. The Clinical Research Center of Xuhui District Central Hospital in Shanghai will conduct regular monitoring tests to ensure the integrity and authenticity of all data. Interim data analysis should not be undertaken for any reason at any time. To ensure the confidentiality of the participants, all patients will be made pseudonymous using study identification numbers. Moreover, all researchers will have access to the final database.

### Quality control and monitoring

This study aims to explore the efficacy and mechanism of rESWT for PDM. The Data Monitoring Board is considered a non-essential safety consideration at this time, and similar studies often apply the same approach. Owing to the heavy variety of data tasks, inspectors must monitor the data. According to the actual situation, they will conduct evaluation of the source documents, including medical document charts, related reports and AE records, as well as additional documents, such as agreements, informed consent forms and pathological report forms, all of which will also be under unified management.

## Discussion

Current first-line guidelines for treating PDM advise the use of nonsteroidal anti-inflammatory drugs or oral contraceptives. However, long-term side effects limit the applicability of such treatments [3]. Complementary and alternative therapies include exercise, acupuncture and percutaneous electrical nerve stimulation. In recent years, acupuncture has been used to treat dysmenorrhoea, and studies have found that it can improve symptoms in women with dysmenorrhea and that it is more effective than traditional Chinese medicine or placebo. Other researchers found no advantage for acupuncture when compared with a placebo [3, 24]. A retrospective analysis confirmed the efficacy of high-frequency percutaneous nerve electrical stimulation for dysmenorrhoea. However, high-frequency electrical stimulation may cause local muscle tension and generate adverse reactions, such as headache, nausea, skin flushing or a burning sensation [3]. Such stimulation is limited in its practical application owing to its obvious side effects, expensive treatment or long treatment cycle, unsatisfactory treatment outcome and for other reasons. Therefore, safer and more effective non-drug analgesic schemes must be explored to control PDM.

As far as we know, this work will be the first randomised clinical trial to evaluate the effects of rESWT on pain relief, mental health and changes in brain function in patients with PDM. Few previous studies have used rESWT as a treatment for PDM and even fewer have investigated the brain function of PDM patients from the perspective of imaging.

This study aims to explore the differences in pain intensity, anxiety, depression, mood and functional brain networks in patients with PDM after rESWT treatment. To accurately elucidate the effect of rESWT, we will compare the changes in MRI indexes in the rESWT group and a sham rESWT group and test whether the changes in pain condition are related to changes in brain function after rESWT treatment. Although previous studies have examined brain function in patients with nervous disorders and abnormal change due to PDM, they only explored the disease itself and did not examine the intervention [23, 25, 26]. To our knowledge, our research will be the first to use MRI to reflect divergence of efficacy of rESWT treatment for PDM and the related neural mechanisms through a randomised controlled trial. Existing research [26] shows that midbrain activity is closely related to the Cox retrospective symptom scale (RSS; *r* = 0.489), and the medial prefrontal cortex activity and RSS showed negative correlation (*r* = −0.580); the medial prefrontal cortex aims to reduce the activity of the brain’s pain-regulating system. Thus, the CMSS was chosen as one of the main outcome measures for this study. This scale is usually employed to evaluate dysmenorrhoea symptoms and to detect the severity of dysmenorrhoea.

The limitations of this trial should be mentioned. A sham radial extracorporeal shock wave group will function as the control group in this study. Since no research is available on reliable treatment using sham shock waves, the principle of controlling with no energy output in previous clinical studies is applied. However, limitations occur with any type of sham shock wave. First, this is not a double-blind trial because those conducting the treatment cannot blindly assign treatment without knowing the type of treatment. To minimise the risk of bias, participants and evaluators will be carefully identified for their shock-wave types and trained in advance to apply a sham shock wave with the machine vibrating and pushing onto the handle with almost no energy. Second, a shock wave often shows a large nonspecific effect and produces physiological activity, which cannot be ignored during the experiment. Nonetheless, the neural mechanisms between different groups can be compared. Therefore, by using the MRI results, we can recognise rESWT-specific pathways related to pain amelioration, even if their effects are not significantly different. Third, a healthy group should not be used as a control group. Previous literature has shown differences in the brain networks of patients with PDM and healthy participants [27, 28]. Conversely, our study will focus on the functional brain changes that will be confirmed by extracorporeal shock wave rather than the PDM-specific features against healthy controls. Therefore, the comparison of the changes in brain networks between the rESWT and sham rESWT groups will be emphasised. Thus far, the randomised controlled trial has only been exploratory, but the prospects look promising. In the future, we expect to collect extensive samples with higher-quality randomised controlled trials.

### Trial status

The study was registered with the Chinese Clinical Trial Register (ChiCTR1900020678) on 13 January 2019. Participant recruited was started on 31 January 2019. At the time of submission, seven patients have been selected into our centre. Recruitment is expected to be completed around December 2019.

## Data Availability

Not applicable.

## Abbreviations

AE: Adverse event
ALFF: Amplitude of low-frequency fluctuation
BOLD: Blood oxygenation level-dependent
CMSS: Cox Menstrual Symptom Scale
DPARSF: Data processing assistant for resting state functional magnetic resonance imaging
fMRI: Functional magnetic resonance imaging
PDM: Primary dysmenorrhoea
rESWT: Radial extracorporeal shock wave therapy
SAE: Serious adverse event
SAS: Self-rating Anxiety Scale
SDS: Self-rating Depression Scale
SF-MPQ: Short form of the McGill Pain Questionnaire
